In each daily session, patients will be gradually verticalized (from supine up to a maximum of 90° upright position), using a combined robotic-assisted tilt table with lower limb mobilization, Erigo^®^ (Hocoma, Volketswil, Switzerland), (VEM group) or conventional non-robotic tilt table (TV group). The robotic device combines verticalization with rhythmic controlled passive alternating loading and unloading of the legs of which protocol (e.g., simple stepping, sinus walking) will be set up depending on the patient’s osteoarticular condition (e.g., range of movement = 45°; pace = 24 steps/min), without functional electric stimulation. Legs stepping movements will be obtained with the rhythmic alternating feet pushing up that will be tailored from complete (100% of assistance) to no (0% of assistance) passive mobilization for each limb according to the patient’s motor and cognitive ability and side effects such as pain (see Appendix A for the list of available tasks). Similarly, patients assigned to the TV group will be gradually verticalized (from supine up to a maximum of 90° upright position), according to the patient’s clinical, motor, and cognitive status, using a traditional tilt table. The verticalization in both arms of the trial, and the stepping frequency, and the percentage of assistance for each leg in VEM, will be tailored based on patients’ vital parameters, tolerance to verticalization, and pain (see outcome measures below). VEM and TV training will be performed with the supervision of a physiotherapist and a physician will be always available in case of emergency. In the robotic arm, blood pressure drops were managed—before tilt reversal—by increasing stepping frequency or encouraging active pedaling in conscious patients. These strategies were not available in the traditional tilt-table group, where blood pressure (BP) recovery relied solely on repositioning.

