During each VEM or TV session, BP, heart rate (HR), and oxygen saturation will be monitored throughout the entire session to prevent complications associated with orthostatism (e.g., hypotension and syncope). In unconscious patients, these vital parameters will be continuously monitored. In conscious patients, they will be recorded at each verticalization step or whenever symptoms or clinical signs potentially indicative of hypotension or cardiac rhythm disturbances occur (e.g., reduced arousal, pallor, nausea). An ad hoc checklist (Adverse Events Report) will be used to record the following possible adverse events (AE), which will also be documented in REDCap: (i) orthostatic hypotension, defined as a sustained drop in systolic BP ≥ 20 mmHg or diastolic BP ≥ 10 mmHg within 3 min of tilt angle change, according to the diagnostic criteria established by the American and European Autonomic Societies [20]; (ii) postural tachycardia syndrome, defined as a sustained HR increase ≥ 30 bpm within 10 min of standing, in the absence of orthostatic hypotension [20]; (iii) bradycardia, defined as HR < 50 bpm; (iv) oxygen desaturation < 90%; (v) signs of excessive pain or clinical discomfort, particularly in patients with pDoC (e.g., agitation, self-removal of medical devices, violent or unsafe movements).

To ensure rapid activation of emergency procedures in the event of AE during verticalization, all patients must have a functioning intravenous access to allow prompt pharmacological intervention if needed. Airway suction, oxygen delivery systems, and a crash cart are readily available; physiotherapists are trained in their use. A nurse and a physician are available on the ward for rapid intervention if required. In the event of orthostatic hypotension, the following steps are implemented: (i) immediate return to the previous tilt angle; (ii) if unresolved, return to 0°; (iii) if hypotension persists, the patient is placed in the Trendelenburg position; (iv) if instability continues, pharmacological treatment is initiated under medical supervision via the pre-established IV access.

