Age between 18 and 75 years; sABI due to traumatic, vascular, anoxic, or mixed etiology; Stable behavioral/cognitive diagnosis on at least 4 behavioral evaluations in 1 week using the Italian version of the CRS-R in patients with pDoC, or the LCF-based cognitive assessment in patients with eDoC; Time post-injury between 28 days and 6 months [1]; Not recovered upright station; Written informed consent by the patient’s legal representative/primary caregiver.	Severe medical conditions hampering verticalization (e.g., severe hypotension or conditions realizing hemodynamic instability, end stage or severe symptomatic heart failure with reduced ejection fraction, cardiac arrhythmia of new diagnosis or arrhythmic flare, severe hepatic failure, chronic severe lower limb arterio-venous disease, sepsis/septic shock, thrombus venous embolism of new diagnosis, severe autonomic dysreflexia); Severe medical conditions hampering lower limb mobilization (e.g., fractures, heterotopic ossifications); Severe medical conditions impacting EEG activity (e.g., sub-continuous or abundant EEG epileptiform abnormalities); Severe medical conditions influencing consciousness/cognitive status, such as severe hyponatremia or hypoglycemia; Contraindications to the use of Erigo^®^Basic and/or Erigo^®^Pro (Hocoma, Volketswil, Switzerland) as per technical data sheet (see Appendix A); Presence of prohibited drugs (see Appendix B).

Abbreviations: CRS-R = Coma Recovery Scale-Revised; eDoC = emergence from Disorder of Consciousness; EEG = electroencephalography; LCF = Level of Cognitive Functioning; pDoC = prolonged Disorder of Consciousness; sABI = severe Acquired Brain Injury.

**Table 3 jcm-14-06628-t003:** Summary of primary, secondary, and exploratory outcomes and measures.

Outcome	Timing, Measure
Primary outcome: Global cognitive functioning	At T0 and T1: LCF
Secondary outcomes:	
Functional disability Spasticity of lower limbs Muscular strength of lower limbs Functional independence Usability of devices from physiotherapists Adverse events	At T0, T1 and T2: DRS At T0, T1 and at T2: MAS At T0, T1 and T2: MRC. Additional clinical observation of spontaneous or reflex movement to pain stimulation in pDoC patients At T0, T1 and T2: mBI At T1: SUS Each daily session: AER
Exploratory outcomes:	

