## Appendix A

**Table A1 jcm-14-06628-t0A1:** List of the tasks available on Erigo^®^Basic and Erigo^®^PRO (Hocoma, Volketswil, Switzerland) and employed for the VEM training. The only difference between Erigo^®^Basic and Erigo^®^PRO is the presence of functional electric stimulation and adjustable hip extension/flexion angle in PRO version, which, however, will not be used in the current trial. Technical data could be found here: https://www.hocoma.com/landing-page/erigo-technical-datasheet-landing/?_gl=1*1onln9k*_up*MQ..*_ga*MTgxOTA2NDQwOS4xNzU0OTIxNjE1*_ga_TJ0VMN8KZJ*czE3NTQ5MjE2MTQkbzEkZzEkdDE3NTQ5MjE2MjMkajUxJGwwJGgw (accessed on 1 September 2025).

Original Name	English Name	Description
Sinus	Sinus	Walking with additional high strike phase, step per minute range from 8 to 80
Andatura	Walking	Walking, step per minute range from 8 to 80
Alternato	Alternate	Simple stepping, step per minute range from 8 to 80

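### The postural tachycardia item has no defined time anchor or reference heart rate on a tilt table, and does not separate leg effort, which the protocol provides for only in VEM

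*Protocol article*

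**What the plan says.** The adverse event checklist in section 2.3.2 of the protocol article has five items. Two are orthostatic:

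- Orthostatic hypotension is a sustained fall of at least 20 mmHg systolic or 10 mmHg diastolic, timed "within 3 min of tilt angle change".
- The next item is "postural tachycardia syndrome, defined as a sustained HR increase ≥ 30 bpm within 10 min of standing, in the absence of orthostatic hypotension".

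On posture, the same section says that in each session "patients will be gradually verticalized (from supine up to a maximum of 90° upright position"; this applies to both arms. Table 2 requires of every patient: "Not recovered upright station".

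On leg activity, stepping in VEM is "tailored from complete (100% of assistance) to no (0% of assistance) passive mobilization for each limb". Blood pressure drops in that arm were handled, before the tilt was reversed, "by increasing stepping frequency or encouraging active pedaling in conscious patients". The section adds that the conventional tilt table offered no such option. Appendix A gives the device's range for each task, for example "Walking, step per minute range from 8 to 80"; the example pace in section 2.3.2 is 24 steps/min.

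Adverse events are a secondary outcome recorded at each session (Table 3) and the only subject of the interim analysis (section 2.6). The Discussion expects fewer side effects in VEM.

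**The concern.** The item leaves two separate things open.

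The first is when the 10-minute window starts and what the rise is measured against. The hypotension item was adapted to the tilt table; the tachycardia item was not. Six centers apply it, and the clinicians and physiotherapists are unblinded (section 2.3.1). If the start is left to local reading, scoring can differ between centers and can depend on the angle a patient reaches.

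The second is effort. Working the legs can raise heart rate, and only VEM includes leg work. A rule whose sole exclusion is hypotension cannot tell an effort-related rise from a postural one. In a comparison of two devices, the item would then measure partly different things in the two arms.

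**Working it through.** The article gives no rate for postural tachycardia, so there is no figure to reproduce. The check is mainly a reading of the text; the arithmetic only shows how far the size is left open.

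**1. Time anchor.** In a stepwise tilt within a 30-minute session, standing could mean the first step, each step, the highest angle reached that day, or 90° only. Take a sustained rise that appears more than 10 minutes after the first step but within 10 minutes of a later one. It scores if the window restarts at each step and does not score if it starts at the first. A patient whose tilt stops short of 90° scores under some readings and never under the last. The hypotension item does not have this ambiguity.

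**2. Reference heart rate.** None is stated. A rise that builds to 30 bpm over several steps scores against the supine value but not against the value at the preceding step.

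**3. Routes by which effort can score.**

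| Situation | Can effort score under the item? | Arm |
|---|---|---|
| Fully assisted, passive stepping | No active effort | VEM |
| Blood pressure drop meeting 20/10 mmHg, then active pedaling | Blocked by the item's own exclusion | VEM |
| Smaller drop, then active pedaling | Yes | VEM only |
| Stepping at low or no assistance, no hypotension | Yes | VEM only |
| Conventional tilt table | No leg-work component | TV |

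**4. Illustration per session (all inputs assumed).** Let the postural rise be normal with mean m and standard deviation SD, and let effort add e bpm. Then P(rise ≥ 30) = 1 − Φ((30 − m − e)/SD).

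| e (bpm) | m = 10, SD = 8 | m = 12, SD = 10 |
|---|---|---|
| 0 | z = 2.5, 0.6% | z = 1.8, 3.6% |
| 5 | z = 1.875, 3.0% | z = 1.3, 9.7% |
| 10 | z = 1.25, 10.6% | z = 0.8, 21.2% |
| 15 | z = 0.625, 26.6% | z = 0.3, 38.2% |

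The rows with e above 0 apply only to sessions with active stepping. The article does not give the share of such sessions.

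**5. Illustration per patient.** Inputs from the article are 25 sessions per patient (section 2.3.2) and 59 patients per arm (Sample Size). Assumed inputs are p, the per-session chance that effort alone meets the rule, and s, the share of VEM patients who step actively. The added share of VEM patients with at least one event is s × [1 − (1 − p)^25].

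- p = 0.2%, s = 25%: 0.25 × 0.049 = 1.2%, or 0.7 of 59.
- p = 1%, s = 50%: 0.50 × 0.222 = 11.1%, or 6.6 of 59 patients and 59 × 0.5 × 25 × 0.01 = 7.4 events.
- p = 5%, s = 100%: 72.3%, or 42.6 of 59.

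In the middle case, with an assumed 10% background in both arms, VEM would show 1 − 0.90 × 0.889 = 20% against 10%. The chance of a significant two-sided difference is then about 33%.

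**6. Net direction.** The Introduction's rationale is that leg mobilization drives venous return and improves cardiac output. If this lowers the postural rise in VEM by k bpm, the net shift is e − k. With k = e, the per-session chance returns to the first row of the table in step 4. With k larger than e, VEM scores fewer events than TV.

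**The case against.** The strongest case against the point is that this is a small wording mismatch. Ninety degrees upright on the table can be read as standing, and the entry criterion on upright station can be read as describing unaided ability rather than position on the device. The effort route is also narrow:

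- Drops that meet the hypotension definition are excluded.
- In conscious patients, vital signs are recorded at each step or on symptoms, so a rise between steps may go unrecorded.
- Stepping frequency and assistance are adjusted to vital signs, which makes a sustained rise of 30 bpm from stepping less likely.
- Eighty steps/min is a device limit, and the article nowhere pairs it with zero assistance.

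A sustained rise caused by the device is arguably a real device effect that belongs in a safety comparison. The item is one of five, and no composite adverse event count is stated.

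Most of this stands and limits the claim. It does not remove it. Reading standing as upright still leaves open which angle counts and what the reference is, and the tilt may stop short of 90°. A narrow effort route is still a route in one arm only. If a device-driven rise deserves reporting, it should be identifiable as such; the checklist item would label it postural.

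A reader might infer that the item can never score because nobody stands on a tilt table. The text does not support that: the anchor is undefined, not impossible. Nor does the one-arm scoring follow from the word standing; it follows from the absence of any separation of effort.

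**Conclusion.** The point holds in limited form. The postural tachycardia item lacks a time anchor suited to a stepwise tilt, does not match the adjacent hypotension item, and states no reference heart rate. It can also score effort-related rises as postural in VEM alone. Fully passive patients, and drops that meet the hypotension criteria, are unaffected by the effort problem.

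A reader might go on to infer that the rule biases the safety comparison against VEM. The documents do not show this. They give no heart rate data, no share of active sessions and no evidence that assisted stepping raises heart rate by a sustained 30 bpm, and their own rationale allows a lower postural rise in VEM. The illustrative range of 0.7 to 43 of 59 patients rests wholly on assumed p and s. It shows that the size is unknown, not that it is large. What is established is that the item, as worded, cannot be compared cleanly between arms.

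**What to change.** For outcome classification only, leaving the management of adverse events unchanged:

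1. Reconcile the two orthostatic items to one tilt-based time anchor and state the reference heart rate, for example the supine value of that session.
2. Keep every qualifying heart rate event recorded as an adverse event in both arms.
3. Add a REDCap flag for leg activity at the time of the event: active pedaling yes or no, assistance percentage, stepping frequency.
4. Report postural tachycardia by arm with and without flagged events.

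Flagging is preferable to taking effort-related rises out of the item. Removal would act on VEM only, so the definition would differ by arm, and it would hide a true postural tachycardia that occurred during active stepping.

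The cost is a short edit to the definition, one or two extra REDCap fields and one more tabulation. Stepping frequency is already among the parameters that the Discussion lists as monitored; assistance percentage is not, so that field would be new.

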In addition, we defined a graded framework for AE seriousness and relatedness to guide session management:-Mild AE: No session suspension required. Symptoms are transient and resolve without intervention (e.g., mild and temporary facial pallor without changes in vital signs);-Moderate AE: Interruption of a single session is required. Symptoms resolve within the same day (e.g., oxygen desaturation resolving after endotracheal suctioning);-Severe AE: Permanent discontinuation of treatment is considered in case of repeated or persistent AE unresponsive to intervention (e.g., hypotension not responding to reduction in tilt angle), or based on medical judgment prioritizing patient safety.

AEs will be managed according to the 90/385/EEC and 93/42/EEC regulations.

A concomitant usual care and rehabilitation interventions will continue without restriction for both arms. Regardless of allocation to the VEM or TV group, all patients will carry out the comprehensive rehabilitation program as designed by the participating center for the entire study period. The usual rehabilitation program consists of alternating bed positioning, passive limb mobilization, cognitive training, activities to facilitate recovery of consciousness (e.g., multisensorial stimulation), speech, and swallowing therapy. During VEM in sABI study, clinicians will be asked to exercise caution when prescribing “prohibited” (i.e., not permitted under the study protocol) and “proscribed” medications (i.e., permitted but requiring careful documentation and, when necessary, adjustment in timing or dosage). These medications may compromise safety (prohibited agents associated with orthostatic hypotension), and affect the interpretability of outcomes by influencing cognition, attention, arousal, or consciousness (proscribed medications) [21,22]. A list of contra-indicated medications and/or cautions is reported in the Appendix B. Information on pharmacological treatments will be collected at baseline and at all follow-up time points.

At the end of the fifth week of treatment (T1), and after 1 month from T1 (T2) a clinical–functional and neurophysiological evaluation will be performed. A serum blood sample will be collected at T2 (see Table 3).

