### 2.6. Statistical Plan

All analyses will be conducted by blinded statisticians. Frequencies (percentages) or mean ± standard deviation will be used for descriptive statistics regarding socio-demographic and clinical variables, as well as for the level of satisfaction with the experimental intervention and the occurrence of side effects.

Given that most outcomes are ordinal or exhibit skewed distributions, we will employ linear or generalized linear mixed-effects models (LMM/GLMM) with appropriate link functions. Ordinal outcomes will be analyzed using cumulative logit mixed-effects models, with random intercepts for patients and for enrolling centers. Continuous outcomes approximately normally distributed will be analyzed with LMM, while skewed continuous outcomes will be modeled with appropriate link functions (e.g., log). All models will adjust for baseline values of the outcome (ANCOVA framework) and include time (T0, T1, T2) and group (VEM, TV) as fixed effects, plus their interaction. Model formulas were defined a priori. The following is an example:logit[P(Y_ij_ ≤ k)] = β_0_ + β_1_Group_i_ + β_2_Time_j_ + β_3_Baseline_i_ + β_4_(Group_i_ × Time_j_) + u_patient(i)_ + u_center(i)_
where u_patient(i)_ and u_center(i)_ are random intercepts for patient and center, respectively.

All analyses will be performed with a two-sided significance level of 0.05. Adjustment for multiple comparisons will be made using Benjamini–Hochberg false discovery rate correction. Statistical analyses will be conducted using R (version 4.4.3; R Foundation for Statistical Computing, Vienna, Austria) or equivalent statistical software. Interim analyses are planned at half of the expected sample for safety outcomes only (i.e., AEs).

Patients violating the VEM-sABI protocol will be excluded from the VEM or TV treatment, but the last clinical observation will be considered for statistical analysis, according to an intention-to-treat approach and a Missing at Random (MAR) assumption inherent to the mixed-model framework. To explore the robustness of the results in scenarios where data may be Missing Not At Random (MNAR), we will conduct pre-specified sensitivity analyses using multiple imputation and, where appropriate, alternative approaches such as joint modeling or delta-adjusted pattern-mixture models.

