Protocol violations include: ex-novo administration or change in dose of proscribed drugs (see list in Appendix B), occurrence of severe AE, transfer to acute wards due to severe medical complications, futility of the intervention (as the patient regains the ability to maintain a 90° upright position for ≥15 min without signs of hemodynamic instability on two consecutive days, combined with functional trunk and lower limb control as reflected by a score of ≥3 in the mBI sub-items “Ambulation”, i.e., constant presence of one or more assistants is required during ambulation, and ≥5 in the sub-item “Stair climbing”, i.e., the patient is able to ascend/descend but is unable to carry walking aids and needs supervision and assistance), missing two consecutive sessions or more than five total sessions or request from patients or their legal representative to withdraw from the study.

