## Figures and Tables

**Figure 1 jcm-14-06628-f001:**
[figure not shown]
CONSORT flow diagram. Abbreviations: sABI = severe Acquired Brain Injury; TV = Traditional Verticalization; VEM = robotic Verticalization and Mobilization.

**Table 1 jcm-14-06628-t001:** Schedule of enrolment, interventions, and assessments from the VEM-sABI study. Each week includes 5 intervention sessions of 30 min duration provided on a daily basis.

Time Point/ Measure	Pre-Randomization	Randomization	Post-Randomization						
	Enrolment	T0 (At the Start of Intervention)	Week 1	Week 2	Week 3	Week 4	Week 5	T1 (After the End of the Intervention)	T2 (1 Month After T1)
Informed consent	X								
Eligibility screening	X								
Allocation		X							
Clinical and anamnestic data collection		X							
Interventions:									
VEM			X	X	X	X	X		
TV			X	X	X	X	X		
Outcomes:									
LCF		X						X	X
CRS-R		X						X	X
mBI		X						X	X
DRS		X						X	X
SUS								X	
MAS		X						X	X
MRC		X						X	X
FDG-CCS		X						X	X
ABS			X	X	X	X	X		
NCS-R			X	X	X	X	X		
30 min standard EEG		X						X	X
Blood sampling		X							X
AER			X	X	X	X	X	X	X

X indicate that activities (rows) are performed at specific time points (columns). Abbreviations: ABS = Agitated Behavior Scale; AER = Adverse Events Report; CRS-R = Coma Recovery Scale-Revised; DRS = Disability Rating Scale; EEG = Electroencephalogram; FDG-CCS = Fondazione Don Gnocchi-Clinical Complication Scale; LCF = Levels of Cognitive Functioning; MAS = Modified Ashworth Scale; MRC = Medical Research Council scale; mBI = modified Barthel Index; NCS-R = Nociception Coma Scale-Revised; SUS = System Usability Scale; TV = Traditional Verticalization; VEM = robotic VErticalization and Mobilization.

**Table 2 jcm-14-06628-t002:** Inclusion and exclusion criteria.

Inclusion Criteria	Exclusion Criteria

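### Patients taken off treatment, for a severe AE or another violation, are analysed at their last clinical observation, which for primary LCF would most naturally be baseline

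*Protocol article*

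**What the plan says.** - **Stopping after a severe AE (Section 2.3.2).** The severe grade reads "Permanent discontinuation of treatment is considered in case of repeated or persistent AE unresponsive to intervention", or stopping may rest on medical judgment. The example given is "hypotension not responding to reduction in tilt angle".
- **Violations (Section 2.6).** The list opens "Protocol violations include: ex-novo administration or change in dose of proscribed drugs (see list in Appendix B), occurrence of severe AE". It goes on to transfer to an acute ward, futility, missed sessions and withdrawal.
- **What happens to violators (Section 2.6).** "Patients violating the VEM-sABI protocol will be excluded from the VEM or TV treatment, but the last clinical observation will be considered for statistical analysis", and this is done "according to an intention-to-treat approach and a Missing at Random (MAR) assumption inherent to the mixed-model framework". The next sentence plans sensitivity analyses for data missing not at random (MNAR).
- **Primary outcome (Table 3).** LCF at T0 and T1. LCF at T2 is exploratory.
- **Visits.** Section 2.3.2 sets the clinical and EEG evaluations as follows: "At the end of the fifth week of treatment (T1), and after 1 month from T1 (T2". Table 1 ("Schedule of enrolment, interventions, and assessments from the VEM-sABI study") marks LCF at T0, T1 and T2. Neither place makes an exception for patients who have stopped treatment.

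**The concern.** The sentence on violators does two things. It takes the patient off the device, and it says which value is analysed. The first is a clinical matter. The second decides the patient's contribution to the primary comparison.

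No LCF is scheduled between T0 and T1. For anyone stopped during the five treatment weeks, the last clinical observation of LCF is most naturally the T0 value. The patient would then count as having made no cognitive gain, whatever happened by T1.

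If such stops are unevenly spread over the arms, the estimated effect of VEM on LCF partly reflects who was stopped. The rule covers every listed violation, including futility stops, where the patient has regained upright posture and may well have improved.

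**Working it through.** The plan gives no severe-AE rate and no figure for the effect of this rule, so there is nothing of its own to reproduce. The check sets the texts side by side and then adds an illustration of sign.

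**1. Which value is last?** Table 3 and Table 1 give LCF at T0, then T1. For a stop between them, the last LCF already recorded is T0.

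**2. Could T1 be observed?** T1 and T2 are scheduled for all patients, with no stated exception. For many stopped patients an observed value should be obtainable.

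**3. Does the rule match the framework it cites?** Intention-to-treat calls for the outcome at the planned time in the arm as randomised, whether or not treatment continued. A mixed model under MAR uses the values observed and needs no substitute for the missing ones. A T0 value entered as T1 is treated by the model as a real T1 measurement. The MAR assumption then does no work for that patient, and no uncertainty is attached to the substitution.

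**4. Can stopping differ by arm?** Section 2.3.2 gives VEM a way to counter a fall in blood pressure before the tilt is reversed (faster stepping, or active pedalling in conscious patients), and says that TV has none. The Discussion expects fewer side effects and fewer related dropouts with VEM.

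**5. Illustration of sign.** Inputs are the LCF gains in the Sample Size subsection. They come from eight weeks of treatment in MCS patients, whereas this trial treats a broader group for five weeks.

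- TV gain: 3.60 - 3.13 = 0.47
- VEM gain: 4.40 - 3.60 = 0.80
- Difference: 0.80 - 0.47 = 0.33

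Assume a severe-AE rate x in VEM and x + d in TV. Every such patient is analysed at baseline and would otherwise have made the arm's mean gain. Then:

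- TV mean change falls by 0.47(x + d)
- VEM mean change falls by 0.80x
- Shift in VEM minus TV = 0.47(x + d) - 0.80x = 0.47d - 0.33x
- The shift is zero at x = (0.47/0.33)d = 1.42d

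| d (assumed) | x (assumed) | Shift in LCF points |
|---|---|---|
| 0.05 | 0 | 0.0235 - 0 = +0.0235 |
| 0.05 | 0.071 | 0 |
| 0.05 | 0.20 | 0.0235 - 0.0660 = -0.0425 |
| 0.15 | 0 | 0.0705 - 0 = +0.0705 |
| 0.15 | 0.20 | 0.0705 - 0.0660 = +0.0045 |
| 0.15 | 0.214 | 0 |

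More stops in TV push the estimate towards VEM. Stops common to both arms push it towards no difference, because VEM has the larger gain to lose. The sign depends on two rates that the documents do not give. The figures are mean changes and do not translate directly into the cumulative logit model planned for ordinal outcomes. All shifts vanish if T1 is measured and used.

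**The case against.** **The sentence need not mean carrying baseline forward.** Beside a MAR mixed model, it could mean only that data up to the last visit are kept. That reading is possible, and it would remove the problem. But the sentence does not say so, and keeping data already collected needs no special rule in a mixed model. The text should settle it.

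**MNAR sensitivity analyses are planned.** They are (multiple imputation and, where appropriate, joint models or delta adjustment), and they count in the plan's favour. They deal with missing values, however. They do not say whether an observed T1 is used, and they do not replace a sound primary analysis.

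**The illustrated effect is small.** The largest shift shown is about 0.07 points on an eight-level scale, with invented rates. That stands, and no larger claim is made.

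**A reader might infer that Sections 2.3.2 and 2.6 contradict each other on stopping,** since one says stopping is considered and the other makes any severe AE a violation with removal. The documents do not prove this. The AE grades are tied to management steps: no suspension, one session interrupted, permanent discontinuation. A severe AE can therefore be read as one that reached the last step, and the sections then agree.

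The hypotension ladder does not decide the matter. After tilt reduction fails, "if hypotension persists, the patient is placed in the Trendelenburg position", and then drugs are given. An episode that resolves there resembles the severe example, but it has also responded to intervention and may fit the moderate grade if it clears the same day. That is a grading ambiguity. It could matter only for a patient graded severe whom the clinician would keep on treatment, and the missed-session or transfer rules might remove many such patients anyway.

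**Conclusion.** The point holds for the analysis rule. As written, patients removed from treatment are analysed at their last clinical observation. For primary LCF and a stop before T1, that is most naturally baseline. This conflicts with the intention-to-treat approach and MAR mixed model named in the same sentence. AE-related stopping may differ by arm, so the treatment contrast could be biased.

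A reader might go further and infer a bias in favour of VEM, because more AE-related stops are expected with TV. The documents do not support a direction. Under the assumptions above the shift runs from about -0.04 to +0.07 LCF points and changes sign within plausible-looking rates.

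The conclusion rests on reading the last observation as a substitute for T1. It has no consequence if T1 is obtained and used. The change should be made because it is cheap and protects the primary analysis. The wording on severe AEs is a secondary clarification, and relabelling the violation alone would change little.

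**What to change.** **In Section 2.6, replace the last-observation wording** with a statement that:

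- patients who stop treatment, for a severe AE or any other listed violation, keep the T1 and T2 assessments at the scheduled times unless consent is withdrawn;
- their observed LCF is analysed in the mixed model by randomised arm;
- no earlier value is carried forward;
- values that are truly missing are handled under MAR, with the MNAR sensitivity analyses already planned.

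**As a secondary clarification,** change the severe-AE entry in the list of violations to treatment discontinuation due to a severe AE, with the reason recorded. It then matches the discretionary wording of Section 2.3.2.

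**Cost.** Some text in Section 2.6. No visits are added, since T1 and T2 are already in Table 1. The small burden is following stopped patients to those visits, some of whom may have been transferred to an acute ward.
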